## Abstract

**Background:**

Neonates with critical congenital heart disease (CCHD) undergoing cardiac surgery with cardiopulmonary bypass (CPB) are at risk of brain injury that may result in adverse neurodevelopment. To date, no therapy is available to improve long-term neurodevelopmental outcomes of CCHD neonates. Allopurinol, a xanthine oxidase inhibitor, prevents the formation of reactive oxygen and nitrogen species, thereby limiting cell damage during reperfusion and reoxygenation to the brain and heart. Animal and neonatal studies suggest that allopurinol reduces hypoxic-ischemic brain injury and is cardioprotective and safe. This trial aims to test the hypothesis that allopurinol administration in CCHD neonates will result in a 20% reduction in moderate to severe ischemic and hemorrhagic brain injury.

**Methods:**

This is a phase III, randomized, quadruple-blinded, placebo-controlled, multicenter trial. Neonates with a prenatal or postnatal CCHD diagnosis requiring cardiac surgery with CPB in the first 4 weeks after birth are eligible to participate. Allopurinol or mannitol-placebo will be administered intravenously in 2 doses early postnatally in neonates diagnosed antenatally and 3 doses perioperatively of 20 mg/kg each in all neonates. The primary outcome is a composite endpoint of moderate/severe ischemic or hemorrhagic brain injury on early postoperative MRI, being too unstable for postoperative MRI, or mortality within 1 month following CPB. A total of 236 patients (*n* = 188 with prenatal diagnosis) is required to demonstrate a reduction of the primary outcome incidence by 20% in the prenatal group and by 9% in the postnatal group (power 80%; overall type 1 error controlled at 5%, two-sided), including 1 interim analysis at *n* = 118 (*n* = 94 with prenatal diagnosis) with the option to stop early for efficacy. Secondary outcomes include preoperative and postoperative brain injury severity, white matter injury volume (MRI), and cardiac function (echocardiography); postnatal and postoperative seizure activity (aEEG) and regional cerebral oxygen saturation (NIRS); neurodevelopment at 3 months (general movements); motor, cognitive, and language development and quality of life at 24 months; and safety and cost-effectiveness of allopurinol.

**Discussion:**

This trial will investigate whether allopurinol administered directly after birth and around cardiac surgery reduces moderate/severe ischemic and hemorrhagic brain injury and improves cardiac function and neurodevelopmental outcome in CCHD neonates.

**Trial registration:**

EudraCT 2017-004596-31. Registered on November 14, 2017. ClinicalTrials.gov NCT04217421. Registered on January 3, 2020

**Supplementary Information:**

The online version contains supplementary material available at 10.1186/s13063-022-06098-y.

## Administrative information

**Table Taba:** 

Title	CeRebrUm and CardIac Protection with ALlopurinol in Neonates with Critical Congenital Heart Disease Requiring Cardiac Surgery with Cardiopulmonary Bypass (CRUCIAL): study protocol of a phase III, randomized, quadruple-blinded, placebo-controlled, Dutch multicenter trial
Trial registration	EudraCT (clinicaltrialsregister.eu) 2017-004596-31, registered November 14, 2017. ClinicalTrials.gov NCT04217421, registered January 3, 2020. All items from the World Health Organization Trial Registration Data Set are included within the protocol.
Protocol version	February 2, 2020, protocol version 2.1.
Funding	This study is funded by ZonMw, as part of the Goed Geneesmiddelen Gebruik, Grote Trials Ronde II program (https://www.zonmw.nl/en/ project number 848042002), the Hartekind foundation (https://www.hartekind.nl), and Friends of the Wilhelmina Children’s Hospital foundation (https://vriendenumcutrecht-wkz.nl).

## Background

Congenital heart disease (CHD) is the most common congenital anomaly in newborns. Critical CHD (CCHD) has an incidence of 3 per 1000 live births and concerns severely ill neonates that require cardiac surgery with cardiopulmonary bypass (CPB) shortly after birth [1]. CCHD includes univentricular heart physiology like hypoplastic left and right heart syndrome; transposition of the great arteries; aortic arch anomalies such as coarctation, interruption, and hypoplasia; truncus arteriosus; total anomalous pulmonary venous connection; and tetralogy of Fallot [1]. Today, 80–90% of CCHD neonates survive until adulthood due to improvements in surgical procedures and perioperative care [2]. Nevertheless, enhancing the quality of life in children growing up with CCHD remains challenging due to long-term neurodevelopmental sequelae, such as cognitive, behavioral, and motor impairments. These sequelae have a financial impact on society, and CCHD is associated with a high number of disability-adjusted life years [3, 4].

Delayed brain development starts already in utero, persists into the neonatal period, and is the result of the underlying cardiovascular defect causing altered cerebral perfusion and reduced oxygenation [5–7]. The underdeveloped brain of CCHD neonates is at high risk for injury early after birth and around cardiac surgery with CPB. White matter injury and strokes with gray matter involvement are commonly observed on magnetic resonance imaging (MRI) and are thought to be the result of hypoxic-ischemic or thromboembolic events [5]. Preoperatively, up to 30% of the CCHD neonates show ischemic brain lesions, while additional injury after cardiac surgery is found in 51% [8].

The cascade to ischemic brain lesions starts with hypoxia, which leads to cerebral energy depletion, excitotoxicity, increased cell influx of calcium, apoptosis, increase in hypoxanthine, and production of pro-radicals [9–11]. After reperfusion and reoxygenation, the enzyme xanthine oxidase (XO) catalyzes the production of superoxide, which normally only accounts for a small part of the produced reactive oxygen species (ROS) [12]. During reperfusion, large quantities of XO are released into the circulation, possibly reacting with plasma purine substrates and molecular oxygen to produce ROS and reactive nitrogen species (RNS), resulting in a state of redox imbalance. This activates an inflammatory response with the formation of pro- and anti-inflammatory cytokines [11, 13, 14]. The development of neuroprotective drugs targeting specific steps in this cascade of events might have the potential to limit hypoxic-ischemic brain lesions [14].

Several perioperative neuroprotective approaches have been explored in the CCHD population. Prior investigated interventions focused on tight glycemic control, alpha-stat versus pH-stat blood gas management, maintenance of high hematocrit levels, cooling, and perfusion techniques such as deep hypothermic circulatory arrest, low flow CPB, and regional cerebral perfusion [15]. Solely maintaining a hematocrit level above 24% during CPB appears to be favorable for the outcome [16–18]. With regard to pharmacological neuroprotection, allopurinol seems the most promising drug in CCHD neonates [19]. Allopurinol, a XO inhibitor, reduces the production of ROS and RNS during reperfusion and reoxygenation [20]. In addition, allopurinol preserves cerebral energy metabolism, is a pro-radical chelator of non-protein bound iron, and has anti-inflammatory properties [21–24].

Prior animal and small neonatal studies suggest neuro- and cardioprotective effects of allopurinol [25]. Clancy et al. showed that the use of perioperative allopurinol resulted in a lower composite rate of clinical seizures, cardiac events, coma, and death in infants with hypoplastic left heart syndrome [26]. During intracardiac repair for tetralogy of Fallot, allopurinol had beneficial effects on the use of inotropes, duration of mechanical ventilation, and intensive care stay [24]. Postnatal administration of allopurinol improved neurodevelopmental outcomes in infants with moderate hypoxic-ischemic encephalopathy [27–29]. Neuronal injury, as measured by S100B and neuroketal levels, was reduced after antenatal administration of allopurinol to fetuses suspected of hypoxia, especially in females. No severe side effects of allopurinol were observed in all previously performed neonatal studies, and neither in the currently ongoing ALBINO Study (NCT03162653) [24, 26–33]. Only in 4.5% of mothers receiving allopurinol, reversible irritation of perivascular tissue was reported after intravenous administration [30].

Previous neuroprotective research in neonatal CCHD focused mainly on interventions exclusively in the perioperative period. However, brain injury occurs already preoperatively [8, 34, 35]. Pretreatment with neuroprotective drugs as allopurinol, which blocks the cascade to ischemic brain lesions, should therefore be administered both early after birth and around cardiac surgery with CPB. Additionally, pre- and postoperative brain MRI are needed to evaluate the effects of postnatal and perioperative treatments on brain lesions separately. Perioperative MRI can be used as a “bridging biomarker” for long-term neurodevelopmental outcomes, since it is known that moderate to severe ischemic brain injury is associated with poorer outcomes at school-age [36].

Therefore, this phase III, randomized, quadruple-blinded, placebo-controlled, multicenter trial will evaluate CeRebrUm and CardIac protection with ALlopurinol in neonates with CCHD Requiring Cardiac Surgery with CPB (CRUCIAL). The aim of this study is to reduce moderate/severe ischemic and hemorrhagic brain injury and improve cardiac function and neurodevelopmental outcomes in CCHD children.

## Methods

The Standard Protocol Items: Recommendations for Interventional Trials (SPIRIT) checklist is provided in Additional file 1 [37].

### Trial design

The proposed study is a phase III, randomized, quadruple-blinded, placebo-controlled, multicenter trial for the superiority of allopurinol versus mannitol-placebo. We hypothesize that allopurinol administration in neonates with CCHD will result in a 20% reduction in the primary outcome, which is defined as the presence of moderate to severe ischemic or hemorrhagic brain injury, being clinically too unstable for postoperative MRI, or mortality.

### Study setting

The trial will be conducted in 4 academic centers for CHD in the Netherlands: University Medical Center (UMC) Utrecht (sponsor), UMC Groningen, and Academic Center for Congenital Heart Disease (ACAHA) in Erasmus Medical Center (MC) Rotterdam and Radboudumc Nijmegen.

### Eligibility criteria

#### Inclusion criteria

Neonates with a prenatally or postnatally confirmed diagnosis of CCHD requiring (anticipated) cardiac surgery with CBP within the first 4 weeks of life are eligible for inclusion. This includes neonates with the following cardiac defects: (1) transposition of the great arteries with or without a ventricular septal defect undergoing arterial switch operation with ventricular septal defect closure if needed; (2) univentricular hearts—hypoplastic left and right heart syndrome or variant undergoing Norwood stage I or Sano palliation; (3) aortic arch anomalies—interrupted, hypoplastic aortic arch, and/or coarctation of the aorta with or without intracardiac defects (ventricular/atrial septal defect or (sub)aortic stenosis) who undergo complete biventricular repair and/or aortic arch repair; and (4) other variants—truncus arteriosus, total anomalous pulmonary venous connection, or tetralogy of Fallot. Written informed consent of both parents is required prior to inclusion.

#### Exclusion criteria

Exclusion criteria include (1) inability to enroll the patient before the start of delivery in case of prenatal diagnosis or 24 h before surgery in case of postnatal diagnosis, (2) uncertainty antenatally whether the heart defect requires cardiac surgery with CPB within the first 4 weeks of life, (3) no anticipated need for CPB during cardiac surgery, (4) gestational age below 36 weeks or a birth weight less than 2000 g, and (5) the patient is deemed incurable or there is a decision of “comfort care only.” Neonates with an underlying syndromic disorder, such as DiGeorge or trisomy 21 syndrome, are not excluded beforehand, as this will not affect the incidence of brain lesions in the composite primary outcome.

### Intervention

Allopurinol 100 mg powder for infusion (PFI) or mannitol-placebo 100 mg PFI is reconstituted in 10 ml sterile water for injection (WFI). Each dose of 20 mg/kg, corresponding to a concentration of 2 ml/kg, will be delivered through peripheral or central line infusion over 10 min using a syringe pump. Blinding is secured as mannitol-placebo PFI has an identical appearance as allopurinol PFI, and with a dose of 20 mg/kg, no clinical effects are expected from mannitol-placebo PFI administration [38]. The study medication will be arranged in patient-dedicated boxes, containing 5 vials of PFI and WFI (prenatal group) or 3 vials of PFI and WFI (postnatal group).

#### Prenatal group

In neonates that are diagnosed with CCHD before birth, allopurinol PFI or mannitol-placebo PFI 20 mg/kg body weight per administration will be administered early postnatally (within 45 (max. 60) min after birth and 12 h after the first dose), preoperatively (12 h prior to cardiac surgery), intraoperatively (at the start of CPB), and postoperatively (24 h after surgery) (Fig. 1).

**Fig. 1 Fig1:**
[figure not shown]
Administration schedule of study medication in both groups. **A** Administration schedule in prenatally diagnosed neonates (prenatal group). **B** Administration schedule in postnatally diagnosed neonates (postnatal group). CCHD, critical congenital heart disease; CPB, cardiopulmonary bypass; h, hours; min, minutes

#### Postnatal group

Neonates in whom CCHD is diagnosed after birth will only receive the pre-, intra-, and postoperative doses of allopurinol PFI or mannitol-placebo PFI (Fig. 1).

#### Randomization and allocation concealment

Randomization will be performed by Ace Pharmaceuticals in blocking for both the prenatal and postnatal diagnosis group (by Randlist version 1.2 software). Stratification will be conducted per center and for a prenatal diagnosis or postnatal diagnosis of CCHD. The first available box of blinded study medication will be allocated by the study team to consecutive study subjects. Each box will be labeled with a unique medication identification number, which enables identification of treatment allocation for data analyses afterwards or emergency unblinding.

#### Adherence to intervention protocol

To improve adherence to the intervention protocol, the study team will organize multiple training sessions for care providers. After completion of the intervention protocol, every patient-dedicated box will return to the study team. Prior to the destruction of the dispensed study medication, an independent monitor will check the drug accountability records.

#### Criteria for discontinuing or modifying allocated interventions

A physician or local principal investigator may decide to terminate the administration of study medication due to safety concerns. The reason for premature discontinuation will be documented, and the outcome of these participants will be included in the intention-to-treat analysis. Parents are allowed to withdraw the participation of their child from the trial at any time. If consent is withdrawn, no further study procedures will be performed. However, we will ask permission to continue data registration for intention-to-treat analysis.

#### Concomitant treatment

Aside from the trial intervention, patients will be treated according to routine clinical practice in each participating center. Administration of open-label allopurinol will not be allowed.

### Outcomes

The period of primary and secondary outcome assessments for every participant will be a total of 24 months.

#### Primary outcome

The primary composite endpoint, assessed within 1 month after neonatal cardiac surgery with CPB, is defined by the presence of moderate/severe ischemic or hemorrhagic parenchymal brain injury on postoperative MRI or being clinically too unstable for postoperative MRI or mortality. All postoperative MRI scans will be assessed centrally and blinded in the UMC Utrecht by 2 experienced neuro-neonatologists. Moderate brain injury is defined as 4–6 white matter lesions < 2 mm or 1–2 lesions 2–4 mm, single focal infarction of the gray matter > 2 mm, or a single hemorrhage (including cerebellar) 2–5 mm. Severe brain injury is defined as > 6 white matter lesions < 2 mm or > 2 lesions 2–4 mm or lesion(s) > 4 mm, infarction with involvement of both the gray and white matter, multiple infarctions of the gray matter, multiple hemorrhages or a single hemorrhage (including cerebellar) > 5 mm, or involvement of the posterior limb of the internal capsule (motor tracts) or radiatio optica (visual tracts) [8]. The patient is deemed “too unstable for postoperative MRI” when the clinical team considers (transport to) MRI too risky due to hemodynamic instability, e.g., need for inotropic support, (septic) shock, or cardiac arrhythmias.

#### Secondary outcomes

The secondary outcomes that will be compared between the allopurinol and mannitol-placebo groups are presented in Table 1 and include the five elements (domain, specific measurement, specific metric, method of aggregation, and time point) as described by Zarin et al. and Saldanha et al. [55, 56].

**Table 1 Tab1:** Secondary outcomes

Domain	Specific measurement	Specific metric	Method of aggregation	Time point
Brain injury severity	Brain injury severity score, determined by the assessment of brain injury on MRI in the deep gray matter, white matter, cortex, and cerebellum [39, 40].	Preoperative brain injury severity score, postoperative brain injury severity score, and change between pre- and postoperative brain injury severity score	Mean (and SD) or median (and IQR) per group	Preoperative (4–7 days after birth) Postoperative (5–10 days after surgery or at least within 1 month after surgery)
White matter injury volume	White matter injury volume (mm^3^), determined by manual segmentation with 3D-Slicer or ITK-SNAP 2.0 [41–43].	Preoperative white matter injury volume, postoperative white matter injury volume, and change between pre- and postoperative white matter injury volume	Mean (and SD) or median (and IQR) per group	Preoperative (4–7 days after birth) Postoperative (5–10 days after surgery or at least within 1 month after surgery)
Echocardiographic systolic and diastolic function	Echocardiographic assessment of global ventricular function (normal, mildly reduced, moderately reduced, severely reduced); ejection fraction (%); shortening fraction (%); ventricular dimensions (mm, *Z*-score corrected for BMI); velocity over the cardiac valves, i.e., *V*peak (m/s) and *V*mean (m/s); cardiac valve insufficiency (no, mild, moderate, severe); longitudinal strain (%) and tissue Doppler imaging (myocardial deformation indices (m/s)); and systolic and diastolic pulmonic vein flow (m/s) [44].	Preoperative echocardiographic measurements, postoperative echocardiographic measurements, and change between pre- and postoperative echocardiographic measurements	Distribution per group for categorical variables and mean (and SD) or median (and IQR) per group for continuous variables	Preoperative (4–7 days after birth) Postoperative (5–10 days after surgery or at least within 1 month after surgery)
Seizure activity	Presence or absence of seizure activity on aEEG [45, 46].	Postnatal seizure activity and postoperative seizure activity	Proportion of neonates with seizure activity per group	Postnatal (until at least 24 h after birth) Postoperative (until at least 48 h after surgery)
Regional cerebral oxygen saturation	Regional cerebral oxygen saturation (%), lowest regional cerebral oxygen saturation (%), and duration of regional cerebral oxygen saturation < 45% (minutes) will be assessed by NIRS in intervals 0–3, 3–6, 6–12, 12–24, and 24–36 h after birth and 0–3, 3–6, 6–12, 12–24, 24–48, and 48–72 h after surgery [47, 48].	Postnatal regional cerebral oxygen saturation, postoperative regional cerebral oxygen saturation, and change between postnatal and postoperative regional cerebral oxygen saturation	Mean (and SD) or median (and IQR) per group	Postnatal (until at least 24 h after birth) Postoperative (until at least 48 h after surgery)
General movements	Assessment of general movements, using the motor optimality score [49–51].	Motor optimality score at 3 months	Mean (and SD) or median (and IQR) per group	3 months
Motor, cognitive, and speech/language development	Motor, cognitive, and language composite score of the Bayley-III-NL. An average Bayley-III-NL score is 100; one SD above or below the mean concerns 15 points [52].	Motor, cognitive, and language composite score at 24 months	Mean (and SD) or median (and IQR) per group and proportion per group below 1 SD	24 months
Quality of life	Parent-reported quality of life score using the TNO-AZL Preschool Children’s Health-Related Quality of Life questionnaire [53].	Parent-reported quality of life score at 24 months	Mean (and SD) or median (and IQR) per group	24 months
Cost-effectiveness of allopurinol	Questionnaires on the need for healthcare resources, productivity losses of parents, and expenses borne by families. Healthcare and societal costs will be determined with the Dutch guidelines for health economic evaluation.	Healthcare and societal costs at 3 months; healthcare and societal costs at 24 months	Mean (and SD) per group	3 months 24 months
Cost-effectiveness of allopurinol	Length of hospitalization and intensive care stay (days) and costs associated with hospitalization using standard unit prices from Dutch guidelines for health economic evaluation.	Healthcare costs	Mean (and SD) per group	24 months
Cost-effectiveness of allopurinol	Motor, cognitive, and language composite score of the Bayley-III-NL [52] and healthcare and societal costs. Healthcare and societal costs will be determined with the Dutch guidelines for health economic evaluation.	Bayley-III-NL score, healthcare, and societal costs	Cost per point improvement in neurodevelopmental outcome per group	24 months
Pharmacokinetic evaluation of allopurinol	Allopurinol, oxypurinol, hypoxanthine, xanthine, and uric acid levels (mg/L) will be measured in blood samples collected around birth and surgery in 24 patients with a prenatal diagnosis [20, 32, 33, 54].	Allopurinol, oxypurinol, hypoxanthine, xanthine, and uric acid levels (mg/L)	Mean (and SD) or median (and IQR)	Postnatal (umbilical cord and 15–60 min, 4 h, 12 h, 13–14 h, 24 h, 36–48 h, and 96–168 h after birth) Perioperative (0–3 h before dose 3, 1–3 h after dose 3, 0–1 h before dose 4, at the end of CPB, 4 h after surgery, 0–3 h before dose 5, 1–3 h after dose 5, and 48 h after surgery)
Redox and antioxidant state of allopurinol	Enzyme-linked immunosorbent assay will be used to measure hypoxic tissue injury, overall redox and antioxidant state, lipid peroxidation, protein oxidation, and nitrosative state. Mass spectrometry will be used to determine allopurinol, oxypurinol, non-protein bound iron, and xanthine oxidase levels (mg/L) [12].	Hypoxic tissue injury, overall redox and antioxidant state, lipid peroxidation, protein oxidation, and nitrosative state Allopurinol, oxypurinol, non-protein bound iron, and xanthine oxidase levels (mg/L)	Mean (and SD) or median (and IQR) per group	Postnatal (umbilical cord) Perioperative (directly before surgery and 6 h, 1 day, 2 days, and 4 days after surgery)

*Abbreviations*: *aEEG* Amplitude-integrated electroencephalography, *Bayley-III-NL* Bayley Scales of Infant and Toddler Development - Third Edition - Dutch Norms, *BMI* body mass index, *CCHD* critical congenital heart disease, *CPB* cardiopulmonary bypass, *IQR* interquartile range, *MRI* magnetic resonance imaging, *NIRS* near-infrared spectroscopy, *SD* standard deviation

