#### Echocardiography

Echocardiography will also be executed pre- and postoperatively, preferably on the same day as the brain MRI, to evaluate potential cardioprotective effects of allopurinol [57]. The echocardiography protocol emphasizes on cardiac systolic and diastolic function, including global ventricular function, ejection (Simpson’s biplane method or four-dimensional) and shortening fraction, ventricular dimensions, velocity over the cardiac valves (pulsed/continuous wave Doppler), cardiac valve insufficiency, longitudinal strain and tissue Doppler imaging (myocardial deformation indices), and systolic and diastolic pulmonic vein flow [44].

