#### Secondary analysis

Secondary analysis is based on the comparisons of secondary outcomes between the allopurinol and mannitol-placebo group, both for the total study population and separately for subgroups of CCHD. Additionally, a secondary analysis will be performed to assess an interaction with gender, as females possibly benefit more from allopurinol administration than males [30]. Descriptive statistics will be applied, including the independent sample *t*-test or the Mann-Whitney *U*-test for continuous data and Pearson’s chi-square test for categorical data. Safety analyses will be based on incidences of (serious) adverse events in both groups.

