#### Risk and benefit assessment

The investigational medicinal products will be studied in neonates with CCHD at high risk of brain injury. CCHD neonates are vulnerable patients who are unable to give consent themselves and are potentially at risk for drug interactions and adverse events of allopurinol. However, the need for pharmacological neuroprotection strategies in this neonatal CCHD population is evident. Previous data suggesting neuro- and cardioprotective effects of neonatal allopurinol doses of 20 mg/kg with low risk of severe side effects should be verified in a large, well-designed trial to prove efficacy or futility. As this trial is placebo-controlled, half of the CCHD neonates will not have a potential beneficial effect of allopurinol. Nevertheless, the use of a placebo agent seems justifiable as study participants often benefit from participating in a randomized controlled trial, considering the potential benefit for future CCHD neonates, and the fact that mannitol-placebo PFI 20 mg/kg is safe [38, 62]. Care is taken to ensure that the study-driven burden for all participants is kept to a minimum.

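### Table 1 scales ventricular dimensions by body mass index, a poor index of a neonate's overall size, so the Z-score keeps avoidable size-related noise; the arm comparison is not biased

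*Protocol article*

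**What the plan says.** In the protocol article, Table 1 under Secondary outcomes lists, within the echocardiography domain, "ventricular dimensions (mm, *Z*-score corrected for BMI"). The abbreviation list under the table reads "BMI* body mass index". The metric is "Preoperative echocardiographic measurements, postoperative echocardiographic measurements, and change between pre- and postoperative echocardiographic measurements".

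The Echocardiography section lists the item again ("shortening fraction, ventricular dimensions, velocity over the cardiac valves (pulsed/continuous wave Doppler")) and names no body-size measure. Body surface area appears nowhere in the article.

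The Secondary analysis section compares continuous outcomes by "independent sample *t*-test or the Mann-Whitney *U*-test for continuous data" and states no covariate for body size. On randomisation the article says "Stratification will be conducted per center and for a prenatal diagnosis or postnatal diagnosis of CCHD", so infant size is not a stratification factor. Eligibility bounds size only from below, by excluding "gestational age below 36 weeks or a birth weight less than 2000 g".

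**The concern.** A Z-score for a heart dimension is meant to remove the part of the dimension that reflects how big the child is. Body mass index divides weight by length squared, so it describes proportion. A small and a large neonate of the same build have the same index but different expected ventricular sizes, and the score treats them alike.

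This is not detail left for another document. The article presents Table 1 as the full definition of each secondary outcome, and the table names a specific scaling variable. No later step described in the article would remove the remaining size variation, since the tests are unadjusted. At stake are the precision of this item and its meaning: a reader will take a Z-score as already corrected for body size.

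**Working it through.** **Plan's own figures.** The article gives no standard deviation, effect size or power for ventricular dimensions, so there is no figure to reproduce for this item. The only design calculation is for the primary outcome. The weighted control rate is (188 × 0.71 + 48 × 0.55)/236 = 67.7%. The weighted allopurinol rate is (188 × 0.51 + 48 × 0.46)/236 = 50.0%. With 118 per arm and two-sided alpha 0.05, power is 79.6%, which agrees with the stated 80% or so. Nothing below changes it.

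**Step 1: what the two indices measure.** BMI = kg/m². BSA = √(kg × cm/3600).

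- 2.5 kg and 45 cm: BMI = 2.5/0.45² = 12.35 kg/m²; BSA = √(2.5 × 45/3600) = 0.177 m².
- 3.6 kg and 54 cm: BMI = 3.6/0.54² = 12.35 kg/m²; BSA = √(3.6 × 54/3600) = 0.232 m².

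The BMI is the same and the BSA differs by a factor of 1.31. Likewise, at a fixed BMI of 13 kg/m², lengths from 43 to 55 cm imply weights from 2.40 to 3.93 kg and BSA from 0.169 to 0.245 m², a 45% spread that the score treats as equal. These examples were chosen to show the mechanism; they do not measure its average effect.

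**Step 2: average effect in a population.** The inputs are assumptions, none of them in the documents: mean weight 3.3 kg (SD 0.45), mean length 50 cm (SD 2.2), weight-length correlation *r* of 0.6 to 0.8, dimension proportional to BSA^0.5, residual coefficient of variation (CV) 8 to 12%. 400,000 infants were simulated per correlation, keeping weights of at least 2 kg and lengths above 42 cm. Log dimension was regressed on log BMI and, separately, on log BSA.

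Variance ratio = (1 − R² for BMI)/(1 − R² for BSA).

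| *r* | CV | R² BSA | R² BMI | Variance ratio |
|---|---|---|---|---|
| 0.6 | 8% | 0.214 | 0.081 | 1.169 |
| 0.6 | 12% | 0.109 | 0.041 | 1.075 |
| 0.7 | 10% | 0.155 | 0.065 | 1.107 |
| 0.8 | 8% | 0.231 | 0.109 | 1.159 |
| 0.8 | 12% | 0.118 | 0.055 | 1.071 |

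First row: (1 − 0.081)/(1 − 0.214) = 0.919/0.786 = 1.169.

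The share of size-related variance that BMI removes is R² BMI/R² BSA. It runs from 0.041/0.109 = 38% to 0.109/0.231 = 47%, so more than half stays in the score. After BMI correction the dimension still correlates 0.19 to 0.30 with BSA. BMI itself correlates 0.61 to 0.68 with BSA, so it is not empty of size information.

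**Step 3: is the arm comparison biased?** The article says that "half of the CCHD neonates will not have a potential beneficial effect of allopurinol", so 1:1 allocation was taken, with 118 per arm. With no true effect, *r* = 0.7 and CV 10%, 4,000 simulated trials gave a mean between-arm difference in the BMI-corrected log dimension of 0.0002 (Monte Carlo standard error 0.0002). There is no bias, only extra scatter.

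**The case against.** The strongest reply is that the matter is small and partly hypothetical. It concerns one item in a long echocardiographic list within a secondary domain. The raw value in millimetres is kept. Ejection fraction, shortening fraction, strain and global function do not use this score. The 1.07 to 1.17 rests wholly on assumed inputs, and because the simulation generates dimensions from body surface area, that measure must come out best. All of this stands, and it limits the size of the point. It does not make weight for length a proper size correction.

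It may also be a slip for body surface area that never reached the planned calculation; an abbreviation list would simply carry the slip along. That cannot be excluded, but the published definition would need the same correction.

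A reader might infer three stronger things, which the documents do not support:

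- *That the treatment comparison is confounded by infant size.* Allocation is randomised and blinded, so size is balanced between arms in expectation, and step 3 shows no bias.
- *That expected dimensions are off by 15%.* The square root of 1.31 is 1.15, but that comes from a pair of infants picked to share one BMI; it does not describe a trial population.
- *That the pre-to-post change is corrupted.* Body surface area also contains weight and would move with early weight change too. Which score moves more depends on the slope of a Z-score reference that is not shown, and in the change each infant is its own control.

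The choice of Z-score reference may be settled in the full echocardiography protocol and is no part of this point.

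**Conclusion.** The point holds as a minor error of definition. Table 1 fixes a scaling variable that tracks neonatal size poorly, and nothing else in the article replaces it. The consequence is a residual variance about 1.07 to 1.17 times as large as with body surface area, or standard errors about 3 to 8% wider (√1.07 = 1.03; √1.17 = 1.08), together with a score that is hard to interpret as size-corrected. These figures depend on the assumed weight and length distributions, the square-root scaling and the residual variation of 8 to 12%. That body mass index measures proportion more than size does not depend on them. The randomised comparison remains unbiased, and the primary outcome and the sample size are unaffected.

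**What to change.** In Table 1, state that the Z-score of ventricular dimensions is corrected for body surface area instead of body mass index, and change the abbreviation list to match. Body surface area is calculated from the same weight and length that body mass index already requires.

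The cost is one phrase in the protocol and a recalculation of the score, best done before unblinding. The recalculation depends on weight and length being available at each echocardiogram. The article does not say that they are recorded then, but the present definition needs them just as much.
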